### Specific aims

 2.1. Primary Aim: Demonstration of a significant (≥ 20%) reduction in the serum levels of interleukin 6 (IL-6)

 2.2. Secondary Aims:

 Improvement in other markers of atherothrombosis and inflammation:

 High sensitivity C-reactive protein (hs-CRP),

 Platelet reactivity

 Adiponectin levels

 IL-1 beta

 Matrix metallo-proteinase 9 (MMP-9)

 Additional exploratory markers including: IL-1 alpha, IL-17, TNF-alpha, MCP-1, monocyte subsets by FACS 

 Safety from hypoglycemic events

 Reduction in glycosylated hemoglobin (Hb A1c)

 Weight reduction

## Investigational plan

### Rationale of study design

The study is designed as a single-center, randomized, non-blinded, clinical trial to provide evidence on the effects of vildagliptin on key biomarkers of atherothrombosis and inflammation. We plan to prospectively enroll 60 patients with proven coronary artery disease and randomize them in a 2:1 ratio to either vildagliptin-metformin therapy (n = 40) or metformin therapy (n = 20). Study design and flow are presented in Figure 1.

**Figure 1 F1:**
[figure not shown]
Figure 1 Study design and flow.

### Rationale of dose, duration of treatment

Vildagliptin-metformin combination is approved by the ministries of health and is commercially available in Israel and Europe. It has been shown to induce significantly less hypoglycemic events and therefore lower sympathetic activation detrimental for cardiac patients. The effects of vildagliptin-metformin combination vs. metformin monotherapy will be assessed 3-months after initiation of therapy. The short duration of the study and frequent follow-up visits with weekly interaction with study personnel will ensure the safe conduct of this trial and improve participant adherence. The 3-month duration has been shown in previous marker centered studies to be sufficiently long to induce the anti-atherothrombotic and anti-atherosclerotic changes. Metformin has been chosen for the comparison group, for the following reasons: 1) the drug was shown to be one of the most efficacious therapeutic options available [23,24]; 2) the clinical experience with the drug is extensive; and 3) it is a component of the comparison group vildagliptin-metformin combination.

### Study population

· Participants eligible for this trial will include male and non-child-bearing potential female patients age 21 years and older who have (a) documented coronary artery disease > 30 day; and (b) evidence of suboptimal type II diabetes control on the basis of Hb A1c ≥7.0%, despite the use of oral antidiabetic monotherapy. Standard of care secondary prevention for coronary artery disease background therapy will include, but will not be limited to, lipid lowering, antihypertensive, beta blockers, and antiplatelet therapy, as appropriate and in accordance to current guidelines.

### Inclusion criteria

· Type 2 diabetes mellitus on oral mono-therapy or diet only treatment

· Stable documented ischemic heart disease (>30 days post AMI, CABG or PCI)

· Suboptimal Hb A1c as defined ≥7.0%

· Age > 21

· Life expectancy >1 year

### Exclusion criteria

· Significant renal impairment (creatinine ≥1.4 mg\dL females or ≥1.5 mg\dL males)

· Planned coronary intervention or planed surgical intervention (PCI or CABG)

· Planned surgical intervention

· Recent (<30 day) acute coronary syndrome (ACS)

· Hypersensitivity to either of the study drug components

· History of lactic acidosis

· Type I diabetes

· Current Hb A1c >9%

· Current Insulin treatment

· Active treatment with GLP-1 or other DPP4i medication

· Hepatic impairment or ALT\AST elevations beyond X2 upper normal limit or known hepatic failure

· Inability to comply with study protocol

· Active malignancy other than basal cell carcinoma

· Clinically advanced congestive heart failure - NYHA III-IV

· Severe left ventricular dysfunction (LVEF < 30%) with NYHA II or any NYHA class with documented recent heart failure decompensation (<3 months)

· Severe stable cardiac angina CCS III – IV or Unstable angina

· Chronic inflammation (i.e. inflammatory bowel disease, lupus, inflammatory arthritis, rheumatoid arthritis) or chronic infection (i.e. chronic diabetic foot infection)

· Pregnancy, lactation or child-bearing potential

### Baseline clinical evaluation

At baseline patients will undergo detailed assessment including: 1) focused medical history, past cardiovascular events and key clinical findings, 2) body mass index (BMI) measurements, 3) physical examination and medication history. Based on current medication patients will be initiate a wash-out period of 2-weeks as described below.

### Prior antidiabetic medication washout

Eligible patients (Hb A1c ≥7% and ≤ 9%) who receive current anti-diabetic monotherapy (not including metformin or a DPP4i) who consent to participate in the study will initially receive substituted antidiabetic treatment with metformin. Prespecified substitution of oral antidiabetic monotherapy is permitted if clinically reasonable and safe. A washout period of two weeks will take place prior to randomization. During this period, treatment with open label metformin will be carried out with blood glucose monitored regularly. Initial dose will be 850 mg once daily, with a dose increase to a maximum of 850 mg TID stabilization to a target of fasting glucose ≤130 mg/dL. For patients eligible for the study who receive current treatment with metformin monotherapy, a dose increase will also be allowed to a maximum of 850 mg TID aiming for stabilization to a target of fasting glucose ≤130 mg/dL.

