**Design:**

We plan to prospectively investigate the effects of dipeptidyl peptidase-4 inhibition with vildagliptin on a number of atherothrombotic markers and adipokines in patients with proven atherosclerosis and type 2 diabetes. The selected markers are: interleukin-6, high sensitivity C reactive protein, interleukin 1-beta, total adiponectin levels, matrix metallo-proteinase 9 and platelet reactivity testing. Sixty eligible patients will be randomized in a 2:1 ratio to vildagliptin/metformin or metformin only treatment, for a 3-month duration treatment. Blood sampling for the proposed investigations will be taken at enrollment and immediately after completion of the study period.

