### High sensitivity C-reactive protein (hs-CRP)

Marker of inflammation with a strong correlation with cardiovascular events even in normolipemic population [9]. Reduction of hs-CRP has been demonstrated with vildagliptin-pioglitazone combination, but data from patients with cardiovascular disease and vildagliptin-metformin combination are lacking [10].

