### Statistical methods and power calculation

Sample size justification: We expect to show an improvement (defined as >20% biomarker reduction between the baseline and 3-month assessment) in ≥3 of the prespecified biomarkers that comprise the primary end point in at least 50% of the patients randomized to combined vildagliptin-metformin therapy and in <10% of the patients randomized to metformin mono-therapy. The proposed sample size is calculated to demonstrate a significant improvement in the intervention group compared to the control group with at least 90% power and a two-sided 5% type 1 error. These requirements are met with a sample size of 60 patients and a 2:1 randomization design: 40 patients in the combined vildagliptin-metformin intervention group and 20 in the metformin monotherapy control group.

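### Two weeks on metformin is not shown to be enough for prior-drug effects on the markers to settle, and the tested-class exclusion has no look-back: the risk is dilution and chance imbalance, not systematic bias between arms

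*Protocol article*

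**What the plan says.** All references are to the protocol article.

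- **Inclusion criteria** admit "Type 2 diabetes mellitus on oral mono-therapy or diet only treatment", with no restriction by drug class.
- **Prior antidiabetic medication washout** moves patients on monotherapy other than metformin or a DPP4 inhibitor to open-label metformin. On timing it says: "A washout period of two weeks will take place prior to randomization". The only stabilisation target given is fasting glucose.
- **Exclusion criteria** bar "Active treatment with GLP-1 or other DPP4i medication". No look-back period is attached.
- **Statistical methods and power calculation** counts improvement per marker within the patient, "defined as >20% biomarker reduction between the baseline and 3-month assessment".
- **Rationale of dose, duration of treatment** holds the article's only statement on marker timing: "The 3-month duration has been shown in previous marker centered studies to be sufficiently long to induce the anti-atherothrombotic and anti-atherosclerotic changes".
- **Randomization** takes place after the two-week metformin period, in both arms alike.
- **Abstract, Design** says when blood is drawn: "Blood sampling for the proposed investigations will be taken at enrollment and immediately after completion of the study period". **Baseline clinical evaluation** describes the baseline work-up first and the start of the washout after it.

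**The concern.** The run-in is set by glucose, but the endpoints are inflammatory, adipokine and platelet markers. If a prior drug acts on one of these and its effect has not settled when the baseline sample is taken, the baseline-to-3-month change mixes study treatment with withdrawal of the earlier drug.

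The article itself treats drug effects on the markers as a problem. Under Treatment and in the Discussion it asks for statins and other background drugs to stay fixed so that changes do not interfere. The Discussion also links sulfonylureas, through hypoglycaemia and sympathetic activation, to proinflammatory effects. Yet the prior antidiabetic drug, which may be a sulfonylurea, is deliberately changed two weeks before allocation.

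For the tested class, current users are kept out, but a patient who stopped recently is not addressed. Such a patient could enter either arm.

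At stake are the sensitivity of a 60-patient comparison, the balance of a small control arm in which each patient is 5 percentage points (1/20), and the reading of any within-arm change. The last matters because the primary aim under Specific aims, a reduction of at least 20% in IL-6, names no comparator.

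**Working it through.** **1. The plan's own figure.** Inputs from Statistical methods and power calculation: responder rates 50% and 10% (the article says below 10%), 40 and 20 patients, two-sided 5%, at least 90% power. With the pooled z-test:

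- mean rate = (20 × 0.10 + 40 × 0.50)/60 = 0.367
- s0 = √[0.367 × 0.633 × (1/20 + 1/40)] = 0.132
- s1 = √[0.10 × 0.90/20 + 0.50 × 0.50/40] = 0.104
- power = Φ[(0.40 − 1.96 × s0)/s1] = Φ(1.36) = 91.4%

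The stated 60 patients reproduce. That figure takes no account of prior therapy.

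**2. What the text says about timing.** Three months is described as long enough for marker changes to appear on treatment. That is a sufficient time for onset. It is not a minimum time, and it says nothing about how fast an effect fades. No other section does. So the article shows neither that two weeks is enough nor that it is too short.

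**3. Expected bias between arms.** Allocation follows a run-in common to both arms, so exposed patients have the same expected share in each. The mean gap is zero.

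**4. Chance imbalance.** The exposed number K is an assumption: 6, 9 or 12 of 60. The number x who fall among the 20 controls is hypergeometric (60, K, 20), and the gap in shares is x/20 − (K − x)/40 = (3x − K)/40, so it moves in steps of 7.5 points.

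| Exposed of 60 (assumed) | SD of gap | P(gap ≥ 15 points) | P(gap > 15 points) |
|---|---|---|---|
| 6 | 8.3 points | 16.5% | 1.3% |
| 9 | 9.9 points | 24.9% | 4.9% |
| 12 | 11.0 points | 30.4% | 8.3% |

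The two right-hand columns differ so much because 15 points falls exactly on a step (two controls more or fewer than expected). The next step is 22.5 points.

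**5. Dilution, as an illustration.** Let f be the exposed share, again assumed.

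- (a) Exposed intervention patients respond at the control rate: intervention rate 0.50 − 0.40f, control rate 0.10.
- (b) Baseline drift turns half of the exposed non-responders into responders in both arms: intervention rate 0.50 + 0.25f, control rate 0.10 + 0.45f.

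| f | Power (a) | Power (b) |
|---|---|---|
| 0 | 91.4% | 91.4% |
| 10% | 84.7% | 85.3% |
| 20% | 75.5% | 78.8% |
| 30% | 64.3% | 72.2% |

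Both scenarios are deliberately strong. They show the direction and a range, not an estimate.

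**6. When the baseline is taken.** If the sample is drawn at enrolment and enrolment precedes the run-in, the measured change also contains withdrawal of the prior drug and the start of metformin. If it is drawn at randomisation, only what is unsettled after two weeks remains. The article can be read either way.

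**The case against.** The strongest case against runs as follows.

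- **Failure of the washout is not shown.** A reader might infer from the 3-month statement that two weeks cannot clear prior effects. The documents do not support this, because the statement concerns onset and no offset time is given. This objection stands.
- **The pioglitazone example is weak.** The section on hs-CRP says "Reduction of hs-CRP has been demonstrated with vildagliptin-pioglitazone combination". A reader might infer that stopping pioglitazone makes hs-CRP rebound. The sentence does not separate the two drugs and says nothing about withdrawal. This also stands, and the point does not rest on it.
- **The tested class is largely handled.** Current users are excluded, and a patient who stopped recently still passes through the two-week run-in. How many such patients exist is unknown. The exact look-back may stand in a full protocol that is not shown. This stands in part: the same list gives time windows for acute coronary syndrome and for heart failure decompensation, but none here.
- **The comparison is randomised.** A reader might infer systematic bias in favour of one arm. With a common run-in before allocation there is none in expectation. This stands.
- **Imbalance in a covariate is not imbalance in the endpoint.** If exposed patients' response probability differed by 30 points (an assumption), a 15-point gap would move the arm contrast by 0.30 × 15 = 4.5 points, against a planned difference of 40. This stands and limits the size of the point.
- **Covariate adjustment is commonly left to an analysis plan.** That is fair. Its absence from the article is not held against it; adjustment is offered only as a remedy.

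**Conclusion.** The concern holds in a limited form. The article allows any oral monotherapy before entry, changes it two weeks before randomisation, gives no look-back for the tested class, and scores a within-patient change. It does not show that two weeks is enough for the markers. The consequences are possible loss of power, chance imbalance in a small control arm, and a within-arm change that cannot be read cleanly as an effect of study treatment.

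The size is unknown, because the share of exposed patients is not given. The imbalance probabilities depend on the assumed 6, 9 or 12 patients and on whether the 15-point step itself is counted. The power figures depend on assumed shares and on strong assumptions about response. The within-arm reading is the most exposed. The Study purpose section does name metformin monotherapy as the comparator, so a between-arm analysis of IL-6 is probably intended, and that would be protected in expectation.

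This is a worthwhile, inexpensive improvement and does not invalidate the design.

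**What to change.** 1. Stratify the randomisation by prior therapy class (metformin / other oral / none), or adjust the analysis for it. The class is available from the medication history at baseline. Keep to these three levels: the planned rates imply only about 0.50 × 40 + 0.10 × 20 = 22 responders, too few to support a long list of covariates.
2. Replace the active-treatment wording with a look-back for DPP4 inhibitors and GLP-1 drugs, counted back from the baseline biomarker sample. The investigators should set and justify its length; the article contains no offset time from which to derive one. Stratification alone would not catch recently stopped users, who would be classed by their current therapy.
3. Reconcile the Abstract's Design paragraph, Exclusion criteria, Baseline clinical evaluation, Prior antidiabetic medication washout and Randomization, so that they agree on which prior exposure is allowed and whether the baseline sample is drawn before or after the run-in.
4. State the primary aim as a comparison between arms, since neither stratification nor adjustment removes a withdrawal effect from a within-arm change.

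Cost: a slightly smaller eligible pool, one stratum or covariate, and some rewording. No extra visit is needed.

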### Stabilization of oral anti-diabetic therapy for eligible patients not on previous therapy

Eligible patients (HbA1C ≥7% and < 9%) not on current antidiabetic therapy who will consent to participate on the study will be initiated with open-label metformin monotherapy for a period of two weeks prior to randomization. During this period, treatment with metformin will be carried out with blood glucose monitored regularly. Initial dose will be 850 mg once daily, with a dose increase to a maximum of 850 mg TID until stabilization to a target of fasting glucose <130 mg/dL.

### Randomization

Randomization will be carried out following a 2-week period of stabilization on metformin mono-therapy as described above. Patients will be randomized in a 2:1 ratio to open label treatment with vildagliptin-metformin therapy or metformin mono-therapy. This study will be non-blinded to patients and treating personnel. All laboratory tests, the major study endpoints, will be performed by professionals blinded to treatment allocation. An interim analysis will be performed after the recruiting 50% of proposed study participants.

### Treatment

The entire study group will be actively treated orally with either metformin (control group) or metformin-vildagliptin combination (intervention group), once or twice daily. No placebo medication is used in this study. The study is open-labeled. Endpoints are mostly laboratory ones, so the un-blinded design will have a minimal effect on the validity of the obtained results.

Treatment will be initiated as follows: (1) in the control arm, metformin dose will be based on the treatment prescribed at the end of the 2 week pre-randomization period; and (2) in the investigational arm, metformin will be replaced with combined metformin-vildagliptin treatment with an initial dose of once daily. Titration to the three times a day is permitted in accordance to investigators clinical judgment in the control arm, while in the metformin-vildagliptin combination, maximal dose will be twice daily.

Study patients and other treating physicians will be asked not to alter antidiabetic medication unless there is justifiable clinical urgency. As statin have proven anti-inflammatory and diverse pleotropic properties, statin type and dose will be recommended to remain fixed during the 3-month study period, unless otherwise clinically indicated.

### Medication titration

Study design permits, based on blood glucose measurements and additional lab test if deemed necessary, modification of the medication dose with the goal of fasting glucose ≤ 130 mg/dl. In the control arm up-titration will be carried out with metformin, and in the treatment arm up-titration will be carried out with vildagliptin-metformin combination. If control of blood glucose cannot be achieved after maximal drug titration and there are repeated (>3) measurements of FPG > 300 mg/dl after nutritional consultation and exercise, the study investigator is encouraged to add antidiabetic treatment according to medical judgment and national guidelines. Deviations from study protocol are to be recorded in detail on appropriate eCRF. With the exception of severe exacerbations in glucose homeostasis noted earlier, all effort is to be made to maintain a stable treatment plan in coordination with the family physician. Patient’s adherence to study medication will be evaluated by pill-count at the follow-up visits.

### Follow-up visits

All patients will be invited for monthly follow-up visits with study coordinators. During these visits we plan to monitor both clinical and adverse events, verify medication compliance and evaluate any hypoglycemic events. Trained medical personnel will verify the home monitoring glucose journal. Changes in weight and in drug regiment will be recorded. At the completion of 3-months blood will be drawn for laboratory testing as done at baseline. Blood samples will not contain identifying information and all tests are to be performed in a blinded fashion.

### Statistical methods and power calculation

Sample size justification: We expect to show an improvement (defined as >20% biomarker reduction between the baseline and 3-month assessment) in ≥3 of the prespecified biomarkers that comprise the primary end point in at least 50% of the patients randomized to combined vildagliptin-metformin therapy and in <10% of the patients randomized to metformin mono-therapy. The proposed sample size is calculated to demonstrate a significant improvement in the intervention group compared to the control group with at least 90% power and a two-sided 5% type 1 error. These requirements are met with a sample size of 60 patients and a 2:1 randomization design: 40 patients in the combined vildagliptin-metformin intervention group and 20 in the metformin monotherapy control group.

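### The protocol cuts each marker to a yes/no fall of more than 20%; marker for marker this loses roughly 40–55% of the information that a baseline-adjusted log-scale analysis of the same samples would use

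*Protocol article*

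**What the plan says.** The only outcome definition in the protocol article's Statistical methods and power calculation section is a per-marker yes/no: "We expect to show an improvement (defined as >20% biomarker reduction between the baseline and 3-month assessment"). A patient counts as improved when this happens "in ≥3 of the prespecified biomarkers that comprise the primary end point". The expected rates are improvement "in at least 50% of the patients randomized to combined vildagliptin-metformin therapy" and "in <10% of the patients randomized to metformin mono-therapy", tested "with at least 90% power and a two-sided 5% type 1 error". The section concludes: "These requirements are met with a sample size of 60 patients and a 2:1 randomization design", that is, 40 and 20.

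Other sections speak of IL-6 and of levels. Study purpose labels IL-6 the primary biological marker among six. The primary aim under Specific aims is a significant (≥20%) "reduction in the serum levels of interleukin 6 (IL-6"). Both values needed for a continuous analysis are collected: "At the completion of 3-months blood will be drawn for laboratory testing as done at baseline" (Follow-up visits), and the abstract's Design paragraph says the same.

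**The concern.** The markers are continuous, and each patient supplies a pair of values for each one. A cut at 20% treats a 21% fall like a 60% fall, and a 19% fall like a rise. It also lets within-person variation alone produce responders in the control arm. With only 20 controls, lost precision matters. A log-scale model with baseline as covariate uses the size of each change and removes chance baseline imbalance for one degree of freedom. It also estimates the quantity that the primary aim describes, a proportional reduction in level. What is at stake is power if the effect is smaller than assumed, and an estimate that can be set directly against the 20% target.

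**Working it through.** **1. The plan's own figure.** Inputs from the sample size section: 50% and 10% (the upper end of the stated control rate), 40 and 20 patients, two-sided 5%.
- Pooled proportion: (40×0.50 + 20×0.10)/60 = 0.367.
- Null SE: √[0.367×0.633×(1/40+1/20)] = 0.1320.
- Alternative SE: √[0.50×0.50/40 + 0.10×0.90/20] = 0.1037.
- Power: Φ[(0.40 − 1.96×0.1320)/0.1037] = Φ(1.36) = 91.4%.

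Exact enumeration gives 92.4% for the uncorrected chi-square and 89.1% for Fisher's test. The stated 60 patients reproduces.

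**2. One marker, 40/20, true 20% fall against no change.** The document gives no marker variability, so these inputs are assumptions: log-normal values, within-person CV of 20%, 30% or 40%, and between-person log SD B of 0.4 to 0.8.
- w² = ln(1+CV²); SD of log change = √(2w²) = 0.280, 0.415, 0.545.
- Control responders: Φ(ln 0.8/SD) = 21%, 30%, 34%. Treated responders: Φ(0) = 50%.
- Log-change power: Φ[0.2231/(SD×√(1/40+1/20)) − 1.96], where 0.2231 = −ln 0.8. At CV 30% this is Φ[0.2231/(0.415×0.274) − 1.96] = 50%.
- ANCOVA: the same formula with residual SD √[(B²+w²)(1−ρ²)], ρ = B²/(B²+w²). At CV 30% the residual SD is 0.377 (B = 0.4) to 0.403 (B = 0.8).

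| Power | CV 20% | CV 30% | CV 40% |
|---|---|---|---|
| Responder, exact chi-square | 60% | 34% | 22% |
| Responder, Fisher | 52% | 26% | 16% |
| Log change | 83% | 50% | 32% |
| Log-scale ANCOVA | 84–87% | 53–58% | 35–40% |

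For a true 30% fall at CV 30%: responder 71%, log change 88%, ANCOVA 90–93%. A second parameterisation (SD of log change 0.3, 0.4, 0.5; baseline to 3-month correlation 0.5; t-based power for ANCOVA) agrees: responder 53%, 34%, 24%; ANCOVA 87%, 64%, 46%.

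**3. Information lost on one marker** (one minus the squared ratio of noncentralities, pooled variance for the responder test). At CV 30%:
- Responder: (0.500−0.295)/√[0.432×0.568×0.075] = 1.51.
- Log change: 1.96, so the loss is 1 − (1.51/1.96)² ≈ 41%.
- ANCOVA: 2.16 (B = 0.4) or 2.02 (B = 0.8), so the loss is 51% or 44%.

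Over the three CVs the loss is 39–46% against log change and 44–54% against ANCOVA.

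**4. Composite against IL-6 alone.** If six independent markers each shift by 20% in the favourable direction at CV 30%, the chance of at least three responses is 25% (control, p = 0.295) and 66% (treated, p = 0.50). The composite chi-square then has 88% power, against 53–58% for ANCOVA of IL-6 alone.

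Starting instead from the protocol's 50% against 10%, simulation of six equally affected markers gives:
- Independent markers: composite about 93%; IL-6 ANCOVA 70–80% (baseline to 3-month correlation 0.7 down to 0.3).
- Markers correlated 0.3: composite 91–92%; IL-6 ANCOVA 92–97%.
- ANCOVA on the mean of all six log markers: above 99% in both cases.
- If the true rates are 30% against 10% (baseline to 3-month correlation 0.5): composite 42–44%; mean of six 92–97%.

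**The case against.** The strongest reply is that the table in step 2 is not about the planned test. The protocol counts patients improving on at least three markers, and on its own assumptions that test has over 90% power. This stands. A reader might infer that the planned comparison has only 22–60% power; the document does not support that, because those figures belong to a single-marker responder test. It also stands that switching to ANCOVA of IL-6 alone could lower power, as step 4 shows.

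Other tempting readings fail as well:
- **The 20% cut defeats itself because only half of treated patients pass at a true 20% fall.** The plan assumes about half and tests the difference between arms, so there is no contradiction.
- **Skewness or raw percent change does harm.** A fall of more than 20% is exactly a log ratio below ln 0.8, so the yes/no result is the same on either scale.
- **Regression to the mean biases the comparison.** Under randomisation it acts on both arms equally in expectation; it adds noise. Adjustment beyond log change gains a modest 3–8 points at CV 30%.
- **Most of the information is discarded.** For one marker against log change the loss is about 40–45%.

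Finally, the responder rule sits in a sample size justification, the primary aim can be read as a change in level, and an analysis plan that is not shown may specify a continuous model. The absence of an ANCOVA specification from a condensed article is therefore not the point here. The point is the outcome that the article does state.

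**Conclusion.** The concern holds as a matter of efficiency. The stated sample size is correct for 50% against 10%. Marker for marker, the cut loses roughly 40–55% of the information. For a true 20% fall that means responder power of about 60%, 34% and 22%, against 84–87%, 53–58% and 35–40% with log-scale ANCOVA, at CVs of 20%, 30% and 40%. The continuous analysis was ahead in every like-for-like scenario tried. The exact size depends on CVs, between-person spread and correlations that the document does not give; the mean-of-six figures also assume equal shifts in all markers.

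It does not follow that the composite is underpowered as planned, or that any continuous analysis beats it. The gain requires comparing the same markers. At the planned 50% against 10% the practical benefit is small (from about 91–93% to above 99%); the protection matters if the effect is smaller.

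**What to change.** - Analyse IL-6 and each other marker by ANCOVA on the log 3-month value, with arm and log baseline as covariates. Report the between-arm geometric mean ratio with a 95% confidence interval.
- Compare the IL-6 ratio with 0.80. For adiponectin an increase is the favourable direction, so that target does not carry over.
- Keep the >20% and three-or-more-marker responder proportions as supporting results.
- If a multi-marker primary is retained, replace the count with a continuous baseline-adjusted combination of all its markers, for example the mean standardised log change with adiponectin sign-reversed.
- If IL-6 is the primary, as Study purpose and Specific aims have it, state the power for its own expected effect and variability. The sponsor must reconcile this choice with the sample size section.

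Cost: wording in the protocol or analysis plan, with no new samples or visits. The stated 90% power must be restated for the chosen primary, and a pooled score or geometric mean ratio is slightly less intuitive than a responder rate. If an existing analysis plan already specifies such a model, the sample size section needs only to be aligned with it.

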## Study design

### Study purpose

To demonstrate that combined vildagliptin-metformin therapy is associated with clinically significant reductions in biological markers of inflammation, pro-thrombogenicity, and atherosclerosis as compared to metformin monotherapy in a population of diabetic patients with coronary artery disease who undergo cardiac rehabilitation.

The prespecified established biological markers of inflammation, pro-thrombogenicity, and atherosclerosis will include: interleukin-6 (IL-6 – primary biological marker), hs-CRP, platelet reactivity testing, MMP-9, interleukin 1 beta (IL-1 beta) and adiponectin levels.

Findings from this analysis will demonstrate the pleiotropic effects of DPP4i in a clinical setting, in addition to its established antiglycemic effects.

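### The primary endpoint is IL-6 alone in the aims but a responder composite of at least three biomarkers in the sample size section, and the stated 90% power belongs only to the composite

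*Protocol article*

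**What the plan says.** Three sections of the Protocol article bear on this.

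- **Study purpose** lists six prespecified markers and singles out one: "interleukin-6 (IL-6 – primary biological marker), hs-CRP, platelet reactivity testing, MMP-9, interleukin 1 beta (IL-1 beta) and adiponectin levels".
- **Specific aims**, item 2.1, gives one primary aim: "Primary Aim: Demonstration of a significant (≥ 20%) reduction in the serum levels of interleukin 6 (IL-6"). Item 2.2 puts hs-CRP, platelet reactivity, adiponectin, IL-1 beta and MMP-9 under the secondary aims, introduced as "Improvement in other markers of atherothrombosis and inflammation".
- **Statistical methods and power calculation** speaks of improvement in at least three of the "prespecified biomarkers that comprise the primary end point", with improvement on a marker "defined as >20% biomarker reduction between the baseline and 3-month assessment". It expects this in at least 50% of the combination arm and fewer than 10% of the metformin arm. It claims at least 90% power at a two-sided 5% level with 40 and 20 patients.

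No other section reconciles these statements, and none gives a power figure for IL-6.

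**The concern.** If IL-6 is the primary endpoint, no patient can improve on three of the biomarkers that make it up. If several biomarkers make it up, five of them cannot also be secondary aims.

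Three things are at stake:

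- **Success criterion.** With two candidates in print, the trial could be called positive on whichever one succeeds, and nothing in the article holds the overall error at 5%.
- **Power claim.** The only power statement is not attached to the only primary aim.
- **Reading of a null result.** A non-significant IL-6 comparison would be taken as coming from a trial with 90% power, which the article does not show.

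**Working it through.** **1. The two definitions side by side**

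| | Specific aims / Study purpose | Statistical methods and power calculation |
|---|---|---|
| Variable | Serum IL-6 | Per-patient count of improved markers |
| Criterion | ≥20% reduction | >20% reduction in ≥3 markers |
| Other five markers | Secondary aims | Part of the primary endpoint, if the six-marker list is meant |
| Power given | None | At least 90% |

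A patient can meet the composite with no fall in IL-6, or have a large fall in IL-6 and miss the composite.

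**2. Reproducing the plan's figure (composite)**

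Inputs from Statistical methods and power calculation: 50% against 10%, 40 and 20 patients, two-sided 5%.

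- Pooled proportion: (0.50×40 + 0.10×20)/60 = 22/60 = 0.367.
- Standard error under no difference: √(0.367×0.633×(1/40 + 1/20)) = 0.132.
- Standard error under the alternative: √(0.50×0.50/40 + 0.10×0.90/20) = 0.1037.
- Power: Φ((0.40 − 1.96×0.132)/0.1037) = Φ(1.36) = 91.4%.

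Solving for 90% power with the same test returns 20 + 40 = 60. Fisher's exact test gives 89.1%. The plan's figure is therefore sound for the composite, and no IL-6 quantity enters it.

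**3. What 40 and 20 patients would give for IL-6**

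The article states no IL-6 SD, so this is illustration. Assumptions: a true between-arm reduction of 20%, so a log ratio of −ln(0.8) = 0.223, analysed as change on the log scale.

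- Power = Φ(0.223/(SD×√(1/40 + 1/20)) − 1.96), where √(1/40 + 1/20) = 0.274.
- SD needed for 90%: 0.223/((1.96 + 1.2816)×0.274) = 0.25.
- SD of log change from a within-person CV: √(2·ln(1 + CV²)).

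| Assumed CV | SD of log change | Power |
|---|---|---|
| 20% | 0.28 | 83% |
| 30% | 0.41 | 50% |
| 40% | 0.55 | 32% |
| 50% | 0.67 | 23% |

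Other assumed scales also spread widely. For a 20-point difference in percentage change, power is 95% at an SD of 20 points, 68% at 30 and 31% at 50.

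The composite rates themselves can also be translated. If six markers responded independently and equally often, rates of 10% and 50% for at least three of six imply single-marker rates of about 20% and 42%. An IL-6 responder comparison at those rates has about 38% power.

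**4. Error rate if either endpoint may count**

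Two independent tests at 5% give 1 − 0.95² = 9.75%. IL-6 may itself be one of the composite's markers, so the tests can overlap. Simulating six independent markers, each with a 30% response in both arms, and comparing IL-6 responders and composite responders by the uncorrected z test, gave about 9.5% for at least one significant result.

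**The case against.** The best reconciling reading is that Study purpose calls IL-6 the "primary biological marker", not the primary endpoint. It lists six prespecified markers, and the sample size section could mean a composite of those six led by IL-6. On those two sections alone that works, and improvement on three markers is then possible. It fails on Specific aims, which states IL-6 as the only primary aim and places the other five under the secondary aims. Nor can this be left to an analysis plan or fuller protocol: it is a conflict between printed statements, and any later document would have to overrule one of them.

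Some narrower objections have force.

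- The article does not announce that both endpoints will be tested as primary. The error inflation describes what the ambiguity permits, not a stated plan.
- 9.75% is the value for independent tests, not a strict ceiling (which is 10%), and positive correlation between the markers would lower it. Overlap through IL-6 alone barely does, as the 9.5% shows.
- The IL-6 powers rest on assumed inputs. The primary aim names no comparator, so a 20% between-arm effect is itself an assumption. They use the SD of an unadjusted change score, and a baseline-adjusted analysis would generally do better. They do not prove that the IL-6 aim is underpowered.
- Laboratory staff are blinded to allocation. That protects the measurements but does not settle which endpoint decides success.

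None of these removes the contradiction or attaches the 90% figure to IL-6.

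**Conclusion.** The point holds and must be fixed. The article gives two incompatible primary endpoints, and its claim of at least 90% power (91.4% on recalculation) applies only to the composite of at least three markers. That conclusion rests on the article's own text and needs no assumption.

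The size of the consequence does depend on assumptions. Power for IL-6 cannot be derived from the article; for a true 20% between-arm reduction it is about 83% to 23% for within-person CVs of 20% to 50%. If either endpoint could carry the claim, the false-positive chance would be about 9.5% to 9.75% under the independence assumptions above, against the nominal 5%.

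**What to change.** Name one primary endpoint and use it identically in Study purpose, Specific aims and Statistical methods and power calculation. Do this before the interim analysis planned at 50% recruitment.

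- **If IL-6 is kept**, as both aims sections have it: define it as the between-arm ratio of 3-month IL-6, tested at two-sided 5%, and make the responder composite secondary. Replace the power sentence with the power, or the detectable IL-6 ratio, that 40 and 20 patients deliver over a stated range of SDs for the analysis chosen.
- **If the composite is preferred**: rewrite aim 2.1 around it and move IL-6 to secondary. List the component markers and the direction that counts as improvement for each. The article's Adiponectin section treats higher levels as protective, so a reduction rule would count the wrong direction for that marker. The existing power figure then stands.

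The cost is protocol wording and, if IL-6 is kept, one recalculated figure that is likely to look less favourable. Neither option by itself requires extra patients.
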